## Methods/Design

### Theoretical foundation

The conceptual framework for the PREPARE intervention and this study has been previously published [15]. In brief, this work rests on the foundation of Social Cognitive Theory, the Interpersonal Communication Competence Model, and Behavior Change Theory [18, 19, 21]. ACP is a complex behavior that often involves people undergoing a series of behavior change steps, which are influenced by knowledge, self-efficacy and readiness. Behavior change is highly influenced by social norms and modeling of these behaviors by others. This framework demonstrates that PREPARE was designed to address important moderator variables such as culture, religion, and literacy. PREPARE incorporates important aspects from the aforementioned theories by including training in communication, goal setting exercises and videos that demonstrate and model ACP behaviors. PREPARE is designed to address modifiable mediators such as knowledge, self-efficacy, and readiness, which then allows individuals to progress through the behavior change stages from pre-contemplation to contemplation and then to readiness and action for the multiple behaviors that compose the process of ACP. Based on the conceptual framework, we developed and validated the ACP Engagement Survey to measure the full construct and process of ACP [22]. Behavioral process measures of behavior change include knowledge, contemplation, self-efficacy, and readiness, whereas ACP actions include identification of a surrogate, identification of values and goals, choosing the level of leeway or flexibility in decision-making for the surrogate, communicating this information with clinicians and surrogate decision makers, and documenting one’s wishes.

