### Measures and data collection

A range of measures are collected to capture the full process of ACP and whether the PREPARE intervention has any effect on ACP, medical decision-making, patient activation, clinician responsiveness, and doctor-patient communication. Table 2 lists all study measures assessed at multiple time points. Details of the main outcome measures are described below.

**Table 2 Tab2:** Constructs and measures for evaluating the efficacy of the PREPARE Study

Construct	Measure	# items	Reliability/validity	Screener	Baseline	1 week	3 month	6 month
	Eligibility screening variables							
Cognitive impairment	Short Portable Mental Status Questionnaire (SPMSQ)	7	Sensitivity 86.2 %, specificity 99.0 % [43]	X				
	0 to 2 = eligible							
	3 to 7 moderate impairment (go on to the Mini Cog three-item recall)							
	≥8 severe impairment = ineligible							
Cognitive impairment (participants scoring 3 to 7 errors on the SPMSQ)	Mini Cog (three-item recall as needed, if SPMSQ screen + for cognitive impairment)	3	Sensitivity 76 %, specificity 89 % [44]	X				
	If recall ≥ two words = eligible							
Vision	Ability to see words on a newspaper [42]	1						
	Moderator variables							
Demographic information	Age, gender, race/ethnicity [45], income, marital status, and education			X	X			
Health literacy screen	“How comfortable are you filling out medical forms by yourself?”	1	AUROC 0.80 (95 % CI = 0.67.0.93) for inadequate health literacy [46]	X				
	“Qué tan seguro (a) se siente al llenar formas usted solo (a)”							
Health literacy assessment	Short form Test of Functional Health Literacy in Adults s-TOFHLA, scores 0 to 36) [47] Continuous & dichotomized to limited = 0 to 22 and adequate = 23 to 36	36	Cronbach’s α = .97		X			
			Correlation coefficient w/ other literacy tests > 0.80 [47]					
United States acculturation	Based on Acculturation scale (USAS) “How many years have you lived in the U.S.?”	1	Cronbach’s α = .98		X			
			Associated w/ desire to know prognosis [48]					
Finances	“In general, how do your finances usually work out at the end of the month?”	1	Associated with functional impairment and comorbidity [49]		X			
Socioeconomic status and social standing	Social standing ladder (that is, place an “x” where you think you stand relative to other people in society)	1	Associated with functional decline [50]		X			

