Functional status	Activities of Daily Living (ADL) and Instrumental Activities of Daily Living (IADL)	15	Morbidity/mortality correlation [51, 52]		X			
Self-rated health status	In general how would you rate your health? (5-pt Likert)	1	Correlation with global health, spearman’s rho = -63, and mortality [53]	X				
Self-rated quality of life	In general, how would you rate your overall quality of life in the past week (5-pt Likert)	1	Test-retest coefficient = 0.81 [54]	X				
Comorbid illness	Determined by ICD-9 codes (chart)	0	Mortality c-stat: [23]		X			
	Charlson comorbidity score [24]		Charlson = 0.704					
	Elixhauser comorbidity score [55]		Elixhauser = 0.793					
Social support	Modified Medical Outcomes Study Social Support (mMOS-SS)	11	Cronbach’s α = 0.88-.93 [56]		X			
Religion/spirituality	Self-reported extent of how spiritual/religious (5-pt Likert) and role play in decision-making.	4	Spirituality associated with quality of life. Religiosity associated with wanting all measures to extend life [57]		X			
Prior ACP experience	Prior ACP experiences (for example, Ever had to make life threatening medical decisions?”) [12]	5			X			
Major life changes	For example, “In the past 6 months, have you or someone close to you been faced with a serious medical problem or diagnosis?”	4						X
	Mediator variables^a^ (also measured as Outcome Variables)							
Baseline knowledge	Knowledge subscales of the ACP Engagement Survey.	6	Cronbach’s α = 0.84 (0.76-0.90), ICC = 0.70 (0.50-0.82) [15]		X			
Baseline self-efficacy	Self-efficacy subscales of the ACP Engagement Survey.	6	Cronbach’s α = 0.83 (0.75-0.89), ICC = 0.60 (0.41-0.76) [15]		X			
Baseline readiness	Readiness subscales of the ACP Engagement Survey.	10	Cronbach’s α = 0.92 (0.88-0.95), ICC = 0.60 (0.53-0.81) [15]		X			
Baseline barriers	Checkbox of 13 common barriers	13	Associated with ACP [25]		X			
Baseline attitudes	Processes of Change for ACP [16]	34	Responsive to an ACP intervention [15]		X			
Desired role in decision-making	Control Preference Scale (CPS) [58]	2	Correlation between preferred and actual role in decision-making [59–61]		X			X
	Primary Outcome Variables							
Full process of ACP	ACP Engagement Survey: Process Measures of knowledge, contemplation, self-efficacy, readiness	116	Process Measures: Cronbach’s α = 0.94 (0.91-0.96), ICC = 0.70 (0.54-0.82) [15]		X	X	X	X
	Action Measures: completion of advance directives, discussions		Action Measures: ICC = 0.87 (0.79-0.92) [15]					

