The sample size of 350 Veterans will also allow adequate power to assess interactions based on potential moderating variables (race/ethnicity, literacy, gender) for our outcomes. We also anticipate very low intra-clinician correlations due to clustering or contamination; randomization is at the patient level not at the clinician level, and intra-clinician correlation values for patient attitudes and knowledge are typically quite low even in physician-level cluster randomized trials (for example, 0.015) [38]. Furthermore, as we have a potential pool of 115 clinicians, most clinicians will care for no more than one to three eligible Veterans and thus, there will be negligible loss of effective sample size accounting for clustering and contamination.

In exploratory analysis to corroborate Veteran reports of activation, we will attempt to recruit 144 surrogates (72 in each arm) anticipating that 20 % of Veterans will not have identified a surrogate based on pilot data, 15 % of Veterans will be lost to follow-up, and 30 % of surrogates will refuse. For patient activation within clinical encounters, we will attempt to audio-record 200 Veterans (100 in each group) to account for potential 25 % of enrolled Veteran and 25 % clinician refusal rates. For input about implementation, we anticipate recruiting 175 Veterans in the PREPARE arm (accounting for a 15 % drop-out at 6 months) and 72 of PREPARE arm Veteran’s surrogates.

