### Data analysis

#### RCT efficacy analysis

Our primary analyses will compare advance directive completion rates and change in engagement in the five ACP behaviors (see Primary outcome section) using behavior change measure scores on a 5-point Likert scale (analyzed as average Likert scores and total scores of 57 to 285) and action measure scores using yes and no responses (scores 0 to 25) from baseline to 1 week, and 3, and 6 months between study arms. We first will use means, medians, and ranges to describe continuous variables, and we will use proportions to describe categorical and dichotomous variables. Baseline comparability of the two groups will then be assessed using t-tests for continuous variables and chi-square tests for proportions. To examine the outcomes between the two study arms longitudinally, we will use mixed effects linear, Poisson, or negative binomial regression for continuous outcome measures and mixed effects logistic regression for dichotomous measures. The mixed effects models will include a random effect for subjects and fixed effects for the primary modeling terms of time, study arm, and an interaction term of study arm and time. We will treat the time variable in three different ways: (i) our first model will encode the time variable as a dummy variable for baseline versus the post-intervention time points; (ii) we will next model time in a continuous linear fashion; (iii) we will lastly consider an arbitrary time course by treating time as a categorical factor variable. We will also adjust for the randomization blocking factors of health literacy (limited versus adequate) and race (white versus non-white) [39] and for any predictor variables that differ between study arms at baseline. We will also include random physician intercepts to account for nesting of patients within physicians. We will consider including random effects for the primary modeling terms of time, study arm, and their interaction. Modeling decisions (for example, which mean structure to use and which random effects to include) will be based on comparing values of the Akaike Information Criterion. Models will be fit using the xt routines in Stata. Mediation analyses will use Stata’s mediation package, which allows estimation of the average causal mediation effect using a potential outcomes framework with either continuous or binary outcomes and allows for sensitivity analyses with respect to violation of the sequential ignorability assumption [40]. Moderating variables will be tested with interaction terms.

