There have been a few logistic challenges to date. Although we attempt to schedule Veteran’s baseline appointment and randomization 1 to 3 weeks prior to their most proximate primary care appointment, this, at times, has been difficult to implement for various reasons. For example, some Veterans reschedule their baseline interview resulting in the intervention occurring within a few days before their clinic visit. Other Veterans or the clinic will cancel a primary care appointment after the baseline interview has occurred resulting in a time frame beyond the three-week ideal. We will adjust for these varying time frames from exposure to the intervention in our analyses. In addition, because the audio-recording occurs at the primary care visit and because several primary outcomes of the study would occur at the primary care visit, we decided to make the primary care visit the date from which all follow-up interviews would be calculated. Because follow-up of the 1-week, 3-month and 6-month interviews within defined time frames was proving challenging, we decided to allow a range of dates that were acceptable. For instance, if a primary care appointment is rescheduled is outside of the ideal 1-3 week window from the baseline interview and randomization, we will audio-record the primary care appointment up to 6 months after the baseline interview, but not after. For the one week follow-up interviews, the allowable Veteran interview range was changed from as early as 5 days from their primary care appointment to as late as 2 weeks prior to their 3-month follow-up; for the 3-month interview the range is from as early as 2.8 months from the primary care appointment to as late as 2 weeks before the 6-month interview; and for their 6-month interview, the ranges is from as early as 5.8 months from the primary care appointment to as late as 9 months from the appointment.

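### Table 2 lists 'Major life changes' as a moderator, but it is asked only at 6 months about a period that falls almost wholly after randomisation, so it should not be tested as an effect modifier

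*Protocol article*

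**What the plan says.** All references are to the protocol article.

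- **Classification.** In Table 2 (Measures and data collection) the four-item row 'Major life changes' stands under the heading "Moderator variables", before the mediator block begins.
- **Content.** One item is shown as an example. With a look-back of 6 months, it asks: "have you or someone close to you been faced with a serious medical problem or diagnosis".
- **Timing.** The row's single mark is in the 6-month column. Every other row under that heading is marked at screening, at baseline, or at both.
- **Analysis.** The RCT efficacy analysis section states: "Moderating variables will be tested with interaction terms". It names no variables and excludes none.
- **Interview window.** The Discussion allows the 6-month interview from "as early as 5.8 months from the primary care appointment to as late as 9 months from the appointment". The visit itself follows the baseline interview, ideally by 1 to 3 weeks (Targeted patient recruitment by phone).
- **Footnote.** The Table 2 footnote about variables that the intervention may change is attached to the mediators only.

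**The concern.** A moderator analysis asks which patients, identifiable when PREPARE is offered, gain more from it. That needs a characteristic fixed before randomisation. A serious diagnosis during follow-up, in the Veteran or someone close, is not known at that time. It may also prompt advance care planning in its own right.

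Three things are at stake:

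1. **Interpretation.** An interaction with this variable could not be used to decide whom to offer the website.
2. **Time order.** The models use outcomes at 1 week, 3 months and 6 months. An event recorded at the end of follow-up may have happened after the earlier outcomes.
3. **Possible bias.** If the arm changes the event, how it is reported, or who stays to report it, then Veterans with and without a reported event are no longer comparable between arms. A false interaction can appear, or a real one can be hidden.

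**Working it through.** The plan gives no power or effect figure for this interaction, so there is none to reproduce. Its attrition figure can be checked: 350 / (1 − 0.15) = 411.8, against the stated target of 410.

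**Step 1. Where the look-back lies.** Measured from randomisation, taken as the day of the baseline interview:

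window opens = lead from baseline to primary care visit + interview time after the visit − 6 months

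Leads are converted at 30.4 days per month: 7 / 30.4 = 0.23 and 21 / 30.4 = 0.69. The Discussion mentions leads of a few days, taken here as 3 days (an assumption): 3 / 30.4 = 0.10. It also allows audio-recorded visits up to 6 months after baseline.

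| Lead | Interview at 5.8 months | Interview at 6 months | Interview at 9 months |
|---|---|---|---|
| 3 days (assumed) | −0.10 | 0.10 | 3.10 |
| 1 week | 0.03 | 0.23 | 3.23 |
| 3 weeks | 0.49 | 0.69 | 3.69 |
| 6 months | 5.80 | 6.00 | 9.00 |

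Only the shortest lead combined with the earliest interview reaches back before randomisation, by about 0.1 month. Everywhere else the window lies wholly after it.

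**Step 2. Time order.** Measured from the visit, the window opens at interview time − 6 months: 5.8 − 6 = −0.2 at the earliest and 9 − 6 = 3 at the latest. For an interview at 9 months, every event in the window comes at least 3 months after the visit. That is later than a 1-week interview held on time, and later than a 3-month interview held between 2.8 and 3 months. For earlier interviews the event may fall before or after those outcomes, and the shown item does not ask which.

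**Step 3. Who has a value.** At the planned 15 % attrition, 410 × 0.15 = 61.5, so about 61 Veterans would lack it. This loss affects every measure taken at the 6-month interview. It matters here because the primary outcome is read from the medical record and may still be available for some of these Veterans, whom the interaction model would drop.

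**Step 4. When bias arises (illustration; all parameters assumed).** Suppose half of Veterans have an unmeasured trait that raises the chance of documentation from 5 % to 25 %, giving 15 % overall in controls. Suppose PREPARE adds 15 points for everyone, so there is no true interaction. The event is reported by 20 % without the trait and 50 % with it.

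Within a reporting stratum, risk difference = 0.15 + 0.20 × (share with the trait in the PREPARE arm − share in the control arm).

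- **Arm does not affect reporting.** The shares are equal, both risk differences are 0.15, and the interaction is 0.
- **PREPARE raises reporting by 10 points in those without the trait (20 % to 30 %).**
  - Event reported: shares 0.5/0.8 = 0.625 and 0.5/0.7 = 0.714; risk difference 0.132.
  - Not reported: 0.5/1.2 = 0.417 and 0.5/1.3 = 0.385; risk difference 0.156.
  - Interaction: −0.024.
- **PREPARE raises it by 20 points (20 % to 40 %).**
  - Event reported: 0.5/0.9 = 0.556 and 0.714; risk difference 0.118.
  - Not reported: 0.5/1.1 = 0.455 and 0.385; risk difference 0.164.
  - Interaction: −0.046.

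The bias is therefore conditional. It is zero if the arm leaves the event, its reporting and retention alone.

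**The case against.** The strongest reply is that no sentence commits the trial to testing this variable. Where the text names moderators, it names others: the sample size text claims "adequate power to assess interactions based on potential moderating variables (race/ethnicity, literacy, gender) for our outcomes", and the theoretical framework says PREPARE was "designed to address important moderator variables such as culture, religion, and literacy". The test follows only from a table heading joined to a general sentence. Table 2's headings are also an imperfect guide: the table puts the ACP Engagement Survey under primary outcomes, while the text makes medical-record documentation primary. The final list of moderators may be settled in an analysis plan that is not shown.

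This limits the weight of the point but does not remove it. Table 2 is the fullest list of moderators in the document, the analysis sentence makes no exception, and the footnote that acknowledges intervention effects does not cover this row. The problem is what the document states, not a detail left for later.

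A reader might infer more than the documents support:

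- **That the interaction is already shown to be biased.** It is not. The shown item concerns events largely external to a planning website, and nothing in the document shows that the arm affects them or their reporting. Such an effect is plausible, because PREPARE encourages talk with family and clinicians.
- **That the answer and the primary outcome come from the same interview.** The primary outcome is taken from the medical record. Only the self-reported outcomes share the interview.
- **That one arm alone was led to think about serious illness.** The Background describes training in communication and decision-making, and both arms review an advance directive.
- **That all four items look back 6 months.** Only one is shown.
- **That the roughly 61 missing values measure this defect.** They are the plan's general attrition.

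**Conclusion.** The point holds as an inconsistency between the moderator label and the time of measurement. As written, the plan treats an essentially post-randomisation variable as an effect modifier. Even without bias, it cannot identify who would benefit from being offered PREPARE, and it may come after outcomes it is said to moderate.

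The size of any false interaction cannot be derived from the document. Under the assumed scenarios it runs from 0 to about −0.05 on the risk-difference scale. The timing result rests on the shown item's look-back, the stated interview window and the intended 1 to 3 week lead. It would weaken for an item with a different look-back.

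One variable in a secondary analysis is affected. The primary comparison and all other main arm comparisons stand. The correction is worth making because it is specific and removes a possible source of bias.

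**What to change.** 1. In Table 2, move 'Major life changes' out of the moderator block and label it as a follow-up variable measured at 6 months.
2. In the RCT efficacy analysis section, state that moderator interaction tests are limited to variables measured at screening or baseline.
3. Report life changes by arm as a descriptive follow-up variable, with the number of Veterans who have a value.

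No substitute moderator is needed: prior ACP experience and comorbidity are already in Table 2 as baseline moderators. A baseline version of the item can no longer be collected, since the Trial status section reports that all 410 Veterans have been recruited. The cost is one table row and one sentence, with no new data.

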#### Measures related to advance directive and ACP documentation

Standard ACP is measured by the completion of advance directives in the VA electronic medical record. We will assess baseline advance directive completion rates and the date the advance directive was signed as well as ACP discussions. At 6 months (date of the last follow-up interview), we reassess the advance directive completion rate and the date it was signed to determine length of time from study enrollment to documentation. An advance directive for the purposes of this study includes the VA or easy-to-read advance directive, a living will, a durable power of attorney for health care document (DPOAHC), a Physicians Orders of Life Sustaining Treatment form, or other documentation of the patient’s wishes for medical care (code status, such as full code or do not resuscitate or do not intubate orders by a physician).

#### Measures related to ACP engagement including behavior change process measures and ACP actions

Full ACP engagement is measured by Veteran self-report at baseline, 1 week, 3 months, and 6 months. Based on Social Cognitive Theory and Behavioral Change Theory [18, 19], we included measures to capture theoretical constructs related to contemplation of behavior, planning or intention to act on the behavior, and the behavior itself. If only the action behavior is measured, such as completion of an advance directive, clinically significant movement along the behavior change pathway will be missed. Thus, it is important to ascertain ACP process measures of behavior change (knowledge, contemplation, self-efficacy, and readiness) for several ACP actions in addition to whether they have completed an ACP behavior (Action Measures). These actions include 1) identifying of a surrogate, 2) identifying values and goals, 3) choosing the level of leeway or flexibility in decision-making for the surrogate, 4) and communicating this information with clinicians and surrogate decision makers, and 5) documenting one’s wishes [22]. As Veterans may have had varying degrees of experience with ACP, we assess baseline engagement in ACP within the past 5 years (standardized based on pilot data). We also ask about engagement in ACP since the randomization date, for example, “Within the past one week, 3 or 6 months”, depending upon the follow-up interval.

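### Self-reported action items: baseline recalls 5 years and follow-up only the time since randomization, so modelled change reflects window length and precision is lost, though the arm comparison stays valid

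*Protocol article*

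**What the plan says.** The section on measures of ACP engagement sets two recall periods. For baseline, "we assess baseline engagement in ACP within the past 5 years". For follow-up, "We also ask about engagement in ACP since the randomization date", with the example wording "Within the past one week, 3 or 6 months" according to the visit.

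The RCT efficacy analysis section compares change in engagement "from baseline to 1 week, and 3, and 6 months between study arms". This includes an action score built from yes/no answers and running from 0 to 25. The mixed models have a random subject effect and "fixed effects for the primary modeling terms of time, study arm, and an interaction term of study arm and time". Time is coded in three ways. For the first, "our first model will encode the time variable as a dummy variable for baseline versus the post-intervention time points", so baseline is a row of the outcome. The second is linear time and the third treats time as categories. Adjustment is planned for the two randomization factors and for predictors that differ between arms at baseline. The baseline value of the outcome is not named as a covariate.

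The Secondary outcomes section adds that each of the five domains will also be analysed as action taken or not taken.

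**The concern.** A change score needs the same quantity at both ends. Here the baseline answer counts actions over 5 years and the follow-up answer counts actions over a week to six months. The two rows carry the same variable name but measure different things, and window length is tied to visit. A fall from baseline, or a rise between 1 week and 6 months, can then arise with no change in behaviour.

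Two things are at stake. First, the time effect and any within-arm change for action items would invite a behavioural reading that they cannot bear. Second, subtracting a baseline that measures something else adds noise to the arm comparison. The same value used as a covariate would remove noise. The article puts change in engagement among its primary analyses under RCT efficacy analysis and calls the secondary outcomes as clinically meaningful as the primary one, so this precision is worth having.

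**Working it through.** **Inputs from the article.** Recall of 5 years at baseline; since randomization, nominally 1 week, 3 months or 6 months, at follow-up. Action score 0-25. 175 per arm, two-sided alpha 0.05. Engagement score with mean 30.7 out of 57 and SD 10. The only within-person correlation for actions is a 7-day test-retest value of 0.87. The correlation r between the 5-year baseline and a follow-up value is not given, so it is an assumption and is shown over a range.

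**1. The plan's own power figure.** The Secondary outcomes section states 80% power for 3 points. SE = 10 × √(2/175) = 1.069; 3/1.069 = 2.806; 2.806 − 1.960 = 0.846; Φ(0.846) = 80.1%. It reproduces, but as a plain comparison of scores between arms with no baseline term, and for the score out of 57. It cannot be moved to the 0-25 action score: the largest possible SD there is 12.5 (half at 0, half at 25), so an SD of 10 would be near the extreme. No SD or target difference for the action score is stated, so no power figure for it follows.

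**2. How much window length alone can do.** Illustrative assumption: a constant rate of action giving 15% in 6 months. Rate = −ln(0.85)/0.5 = 0.325 per year, and the share answering yes over a window of t years is 1 − exp(−0.325t).

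| Window | Yes |
|---|---|
| 1 week | 0.6% |
| 3 months | 7.8% |
| 6 months | 15.0% |
| 5 years | 80.3% |

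Unchanged behaviour therefore shows a steep fall after baseline and then a rise.

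**3. Is the arm contrast biased?** Let w be the shift caused by the windows and d the treatment effect. Expected change is w in controls and w + d in the PREPARE arm; the difference is d. A simulation agrees: 4,000 data sets per setting, 175 per arm, SD 10, control mean 31 at baseline and 12 at follow-up, r = 0.2 and 0.6. Control change was −19. The difference in change was 3.0 for a true 3 and about 0 for a true 0, with type I error about 5%. This was checked on the linear scale.

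**4. Precision, one follow-up, equal variances σ².**
- Difference in change: variance proportional to 2σ²(1 − r).
- Baseline as covariate: σ²(1 − r²).
- Follow-up score alone: σ².

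| r | Change v covariate, 2/(1+r) | Change v follow-up alone, 2(1−r) |
|---|---|---|
| 0 | 2.00 | 2.00 |
| 0.2 | 1.67 | 1.60 |
| 0.5 | 1.33 | 1.00 |
| 0.7 | 1.18 | 0.60 |
| 0.87 | 1.07 | 0.26 |

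The first ratio exceeds 1 for every r below 1. The second exceeds 1 only when r < 0.5.

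**5. Unequal variances.** Different windows may well give different SDs, σ0 at baseline and σ1 at follow-up. Then (σ0² + σ1² − 2rσ0σ1) − σ1²(1 − r²) = (σ0 − rσ1)², which is never negative. The direction of the result does not need equal variances; the size does.

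**6. Three follow-ups pooled**, as the first time coding does, with all correlations equal to r: the ratio is 4/(1 + 3r), that is 4/1.6 = 2.5 at r = 0.2 and 4/2.5 = 1.6 at r = 0.5. Pooling does not remove the loss.

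**The case against.** The strongest reply is that nothing in the randomized comparison is wrong. Both arms answer the same questions over the same windows, the article compares outcomes between arms, and it nowhere announces within-arm change as a result. This stands. A reader might infer that the mismatched windows bias the treatment effect; step 3 shows that they do not.

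A reader might also infer a concrete loss of power by putting the 3-point difference and SD 10 into the change formula. The documents do not support that: those figures belong to the score out of 57, and r is unknown. A low r is plausible across such different windows but is not documented. The 0.87 is a 7-day retest and cannot be carried over either.

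The one-follow-up formula is also simpler than the planned mixed models, which may be Poisson, negative binomial or logistic. It gives the direction and rough size on the linear scale, no more.

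The article does not say how an action completed before enrolment is scored at follow-up. A move from yes to no is therefore an inference from the recall wording, and an item-level rule may exist in documents not shown.

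Finally, part of the remedy is already present: recall since randomization, and time as categories in the third coding. What the reply leaves unanswered is that the model described puts baseline in as an outcome row and does not name it as a covariate.

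**Conclusion.** The point holds in a limited form. For the self-reported action items, the article measures baseline and follow-up over different windows and models them as one repeated outcome. The arm-by-time contrast remains a valid comparison of the arms. Within-arm change and the time trend largely reflect window length and should not be interpreted.

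The cost is precision. Relative to baseline adjustment, the variance is inflated by 2/(1+r), from 2.00 at r=0 to 1.07 at r=0.87, assuming one follow-up and equal variances. Relative to follow-up scores alone, there is a loss only if r<0.5 under the same assumptions. The size therefore rests on a correlation that the article does not give.

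The primary outcome as defined in the Primary outcome section, documentation in the medical record, does not use these recall windows and is unaffected. The process measures are not shown to be recall counts, so the point does not extend to them. This is an improvement available at almost no cost, not the correction of an invalid analysis.

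**What to change.** For the 0-25 action score and the five yes/no domains:

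- Model only the post-randomization visits as outcomes.
- Include the 5-year baseline value as a covariate, in addition to the two randomization factors.
- Use the categorical time coding already listed as the third option, and estimate the arm difference at each visit.
- State that change from the 5-year baseline, and the time trend across visits, will not be interpreted for these items.

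The cost is a change of wording in the analysis section. Table 2 already schedules the engagement survey at baseline and at all three follow-ups, so no new data item is needed. The models for medical-record documentation need no change on this account, and nothing here requires a change for the process measures.
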